## Detailed Study Procedure

A detailed flowchart of the study procedure is presented in Figure 3.

**Figure 3 F3:**
[figure not shown]
Study flowchart.

### Pre-assessment T1 and Assessment of Eligibility

After an initial screening of eligibility for an as early and effective as possible selection of patients and their families and a regular intake consultation with the patient in the outpatient clinic, the patients and their families (children over the age of 6 years) are invited to an informational session at the study center. During this session, the families are informed about the study procedure before signing their consent to participate in the study. For pseudonymized data collection, each participant is assigned a Screening-ID. To assess a broad range of DSM-5 based psychological disorders and comorbid ones as well as severity ratings, structured clinical interviews for patients (DIPS), and children (Kinder-DIPS parent version or SIVA) are conducted with the patient respectively a parent (for each child separately). The parent, with whom the Kinder-DIPS/SIVA is conducted, has to be the same for all children of a family at all measurement points. The in- and exclusion criteria are checked on the basis of the information collected during the screening and the diagnoses based on the clinical interviews. Feedback to diagnoses is given in a separate session. If a patient and its family fulfill all the in- and none of the exclusion criteria, the family is included in the trial and records for the eCRF are created for all the included family members. The family is invited to another session in which interviews about knowledge about mental disorders are conducted with each included family member. After this session codes are handed out with which the family members can log into REDCap at home to complete the questionnaires. Forms with REDCap-codes for the children's caregivers or teachers (one caregiver/teacher for each included child) are also handed out to the family with the request to forward them to the respective caregiver/teachers. There is no reference to the clinical trial of the COMPARE-family project on the caregiver/teacher's form; rather, the questionnaire is generally presented as part of a study at the department of psychology the UMR. After the final inclusion in the study, the randomization to one of the two treatment arms (CBT or CBT+Triple P) takes place. If needed, further probatory sessions can take place at the study centers. In a separate feedback session, the patient is informed about the treatment condition and results of the diagnostic process.

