### Interventions

All patients will receive between 25 (short-term) and 45 (long-term) weekly or bi-weekly sessions of individual state of the art Cognitive Behavioral Therapy (CBT). A high frequency therapy with more than one session per week is also allowed. Depending on the amount and the frequency of therapy sessions, the treatment will usually last between 6 and 12 months. The number of sessions and therapy duration will be documented, thus, allowing us to include therapy duration and number of sessions as a moderating factor in the analyses.

CBT can be considered the current “treatment of choice” for mental disorders in general (32). Central elements are psychoeducation that provides a framework for psychotherapy, cognitive components (i.e., debate of dysfunctional cognitions alias Beck), as well as behavioral interventions (i.e., exposure). As all study sites are outpatient clinics for research and teaching located at university psychology departments, they commit to the highest possible state of the art standard for CBT as outlined in “proceedings in psychotherapy/Fortschritte der Psychotherapie” of which [name] (Co-PI of COMPARE-family) is an editor (33). As the study shall be conducted as naturalistic as possible and a broad range of disorders shall be included, no specific study manual has been created, rather, the respective therapy manuals of the proceedings in psychotherapy will be used in this study.

Patients randomized to the experimental group will receive 8–10 additional group or individual sessions of the Positive Parenting Program (Triple P) parallel to the last third of the psychotherapy sessions to test whether the enhancement of parenting skills will result in improved child outcome, as suggested in different studies (17, 18, 20, 27, 28), above and beyond parental CBT. Triple P is a well-established, widely used and evidence-based program to enhance parenting skills. The Triple P Kids program can be used in groups or individual sessions with parents of children aged 0–12 years (34, 35) and the Triple P Teens program in groups with parents of children aged 12–16 years (36). The Triple P elements are: (1) promotion of a positive parenting style, (2) promotion of child development, (3) dealing with problem behavior, (4) behavior training sessions (34–36).

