### Sample Size

The sample size calculation is based on the primary outcome measure (change in TRF score between T2 and T3) which is hierarchically ranked on top of the multiple testing procedure. Based on the results described above (14, 15, 64), it is assumed that the standardized treatment effect for this outcome expressed by Cohen's d amounts to d = 0.25. With a two-sided significance level of α = 0.05 and a power of 1–β = 0.8 using a two-sample *t*-test, 253 patients per group (*n* = 506 in total) are required. Since the primary outcome is measured on the child level and it is possible to enroll multiple children per patient, a hierarchical multi-level model with patients at level 1 and children at level 2 will be fitted. Taking a drop-out rate of 20 % into account, *n* = 634 patients need to be enrolled into the trial in the analysis. This attrition rate is conservative and based on results from the longitudinal STAR^*^D study that also carried out long-term follow-up assessments (13), as well as on other studies in the field that report even lower attrition rates (65, 66). The problem of attrition and missing values will also be addressed in the analysis by applying the intention-to-treat principle. For missing values, imputation techniques will be applied, thus partly resolving this problem. Since it is assumed that parts of the outcome variance can be explained by the inclusion of covariates, the actual power of the analysis by a linear multi-level model is expected to be higher than 1–β = 0.8. Assuming that the number of children enrolled per patient amounts to 1.5, we expect that *n* = 950 children will participate in the trial. The enrollment of more than one child per patient is expected to yield an additionally increased power. Sample size calculation was performed using SAS v9.4 (SAS Institute, Cary, NC).

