### Statistical Methods

Our primary efficacy analysis will be based on the full analysis set (FAS) according to the intention-to-treat (ITT) principle, reflecting the recommendations given in relevant guidelines (67). The FAS is defined to include all patients enrolled who are assigned to the treatment group they were originally randomized to, regardless of whether they actually underwent the assigned treatment or not. This will be the primary population for evaluating all efficacy endpoints and subject characteristics. Additionally, the per-protocol (PP) population, including all FAS patients with no major protocol deviations, will serve as a secondary analysis population and be used for sensitivity analyses. Before lock of the database, each patient's allocation to the FAS or PP population will be defined in the statistical analysis plan.

The two hypotheses to be assessed in the primary efficacy analysis are ordered hierarchically: In the first step, the null hypothesis ${\text{H}}_{0}^{\text{I}}$: $\mu_{\text{CBT}+\text{PPP}}^{\text{T}3-\text{T}2}$ = $\mu_{\text{CBT}}^{\text{T}3-\text{T}2}$ for the primary outcome “change in teacher CBCL (Teacher Report Form/TRF) score between T2 and T3” is tested at the two-sided significance level of 5% against the alternative ${\text{H}}_{1}^{\text{I}}$: $\mu_{\text{CBT}+\text{PPP}}^{\text{T}3-\text{T}2}$ ≠ $\mu_{\text{CBT}}^{\text{T}3-\text{T}2}$. If ${\text{H}}_{0}^{\text{I}}$ can be rejected, the null hypothesis ${\text{H}}_{0}^{\text{II}}$: $\mu_{\text{CBT}+\text{PPP}}^{\text{T}4-\text{T}2}$ = $\mu_{\text{CBT}}^{\text{T}4-\text{T}2}$ for the second primary endpoint “change in TRF score between T2 and T4” is tested at the two-sided level of 5% against its alternative ${\text{H}}_{1}^{\text{II}}$: $\mu_{\text{CBT}+\text{PPP}}^{\text{T}4-\text{T}2}$ ≠ $\mu_{\text{CBT}}^{\text{T}4-\text{T}2}$. Application of this multiple test procedure for a priori ordered hypotheses ensures control of the family-wise type I error rate at a level of 5%. The null hypotheses will be assessed using a linear mixed multi-level model with patients at level 1 and children at level 2, adjusting for center, number of comorbidities, number of children, baseline TRF score at T2, and length of waiting period between T1 and T2 (in weeks).

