### Pre-assessment T2

After the usual waiting period for a psychotherapy treatment in the study centers (waiting period can differ between the study centers depending on their usual waiting periods for a psychotherapy treatment), structured clinical interviews for patients and children are conducted again with the patient respectively the same parent as in T1 (for each child separately). The family is invited to another session in which interviews about knowledge of mental disorders are conducted with each included family member, and codes for logging into REDCap at home to complete the questionnaires are handed out. The forms with REDCap-codes for the children's caregivers/teachers are also handed out to the family with the request to forward them to the respective caregivers/teachers.

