### Limitations

COMPARE-family plans four extensive assessments for all family members as well as up to 55 therapy assessments. Even though the majority of patients has positive attitudes toward extensive diagnostic assessments (80), this might also be a burden on the family, especially as the add-on projects require additional assessments at the same assessment times.

The implementation of a self-wait control design in the RCT was originally planned with a waiting period of 6 months between the first assessment of the patients and their families and the beginning of the therapy. Due to the new psychotherapy guidelines in Germany, that became effective in April 2017, the waiting periods to receive psychotherapy treatment have decreased enormously at the study sites. Although the time span to receive a place in a treatment program can still be up to 9 months, many of the recruiting outpatient clinics have tried to cut those time spans down (e.g., 1–3 months waiting periods). With the original 6 months waiting period, patients wanting to participate in the COMPARE study would consequently have had to wait longer for their psychotherapy treatment than necessary. For the study centers this not only created ethical but also practical issues with interested patients preferring treatments with shorter waiting periods to the participation in COMPARE. With the now implemented multiple baseline design, the waiting period can vary between the study centers depending on the usual waiting periods on-site, therefore not disadvantaging study participants.

The observation period of only 39 months in total is rather short for capturing effects on the prevention of SMI, but due to funding, a longer observation period could not be implemented. For assessing long-term effects, a follow-up study is already planned and all participants are asked permission to be contacted again later on.

The majority of outpatient clinics will most likely treat patients with depressive and affective disorders, a fact possibly hampering the aim of the COMPARE study to cover a broad range of disorders. However, as all outpatient clinics are university-based and all recruiting centers have different research foci, chances are good that the range of disorders will be represented. This will also raise the generalizability of findings.

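### Randomisation and disclosure of the arm to the patient come at T1, so the T2 baseline of both primary endpoints, and two model covariates, are recorded after allocation

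*Protocol article*

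**What the plan says.** The order of events is set out in Detailed Study Procedure. Under Pre-assessment T1 and Assessment of Eligibility, after the interviews and the handing out of questionnaire codes and teacher forms, the text reads: "After the final inclusion in the study, the randomization to one of the two treatment arms (CBT or CBT+Triple P) takes place". The same paragraph ends: "In a separate feedback session, the patient is informed about the treatment condition and results of the diagnostic process". The next section, Pre-assessment T2, opens with: "After the usual waiting period for a psychotherapy treatment in the study centers". At that visit the family again receives the teacher's form to pass on.

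The Limitations section gives the length of the wait. Its upper end is stated as follows: "Although the time span to receive a place in a treatment program can still be up to 9 months". Shorter waits, of 1 to 3 months, are given there as an example of what many of the clinics now aim for.

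The Primary Outcome Measure section defines both primary endpoints as TRF change from T2, first to T3 and then to T4. Among the adjustment terms of the model in Statistical Methods are "baseline TRF score at T2, and length of waiting period between T1 and T2 (in weeks"); the others are center and the counts of children and comorbidities. The same covariates, plus treatment group, feed the multiple imputation. A TRF is also collected at T1 (Table 1), but it is neither the baseline nor a listed covariate.

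The only treatment difference, Triple P, is given "parallel to the last third of the psychotherapy sessions" (Interventions).

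**The concern.** A baseline that is subtracted from the outcome, or adjusted for, should be fixed before allocation, so that it cannot carry any consequence of allocation. Here it is taken after a wait during which the patient knows the arm. An arm difference could in principle arise by T2 through expectation, parenting help sought elsewhere, selective forwarding of the teacher's form, or leaving the study. Part of any such difference would be removed from the estimated effect if it ran in the same direction, or added to it if it ran the other way.

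There is also a missing-data side. The full analysis set is all enrolled patients as randomised. A family that leaves during the wait is in that set without a T2 score. The one TRF it may have, from T1, is not among the variables listed for imputation.

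**Working it through.** **1. Order of events.**

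| Step | Where stated | Relative to allocation |
|---|---|---|
| T1 interviews; T1 teacher forms handed out | Pre-assessment T1 | described before |
| Randomisation | Pre-assessment T1 | – |
| Patient told the arm (session undated) | Pre-assessment T1 | after |
| Wait, 1–3 and up to 9 months | Limitations | mostly or wholly after |
| T2 TRF: baseline and covariate | Pre-assessment T2; Statistical Methods | after |
| Realised T1–T2 wait: covariate | Statistical Methods | known only after |
| Triple P starts, last third of CBT | Interventions | after T2 |

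No section places randomisation or disclosure after T2. The interval from allocation to T2 is somewhat shorter than T1–T2, because T1 itself takes several sessions.

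**2. The plan's own sample size.** With d = 0.25, two-sided α = 0.05 and power 0.80, the normal approximation gives n = 2(1.960 + 0.842)²/0.25² ≈ 251.2, so 252 per arm. The two-sample t-test gives 252.13, so 253 per arm (power 0.801). With 20% drop-out, 253/0.8 = 316.25, so 317 per arm and 634 in total. The stated figures reproduce, and the timing point does not alter them.

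**3. Effect of an arm difference at T2.** Scale T2 and T3 to SD 1, with within-arm correlation r. Let Δ be the arm difference at T3 and s the arm difference at T2, with s positive when it runs in the direction of the effect. Regressing T3 on arm and T2 gives an arm coefficient of Δ − r·s. Regressing the change T3 − T2 on the same terms has slope r − 1 on T2 and gives (Δ − s) − (r − 1)s = Δ − r·s, the same value. The shift is therefore −r·s.

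The document gives neither s nor r. The table assumes s = 0, 0.05 or 0.10 and r = 0.3, 0.5 or 0.7, with 253 per arm, one child per patient, residual SD √(1 − r²) and Δ = 0.25. The last column sets Δ = 0.

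| r | s | Shift (SD) | Share of 0.25 | Power | Rejection rate if Δ = 0 |
|---|---|---|---|---|---|
| 0.3 | 0 | 0 | 0% | 0.838 | 0.050 |
| 0.3 | 0.05 | 0.015 | 6% | 0.791 | 0.0536 |
| 0.3 | 0.10 | 0.030 | 12% | 0.737 | 0.0645 |
| 0.5 | 0 | 0 | 0% | 0.901 | 0.050 |
| 0.5 | 0.05 | 0.025 | 10% | 0.832 | 0.0622 |
| 0.5 | 0.10 | 0.050 | 20% | 0.738 | 0.0995 |
| 0.7 | 0 | 0 | 0% | 0.976 | 0.050 |
| 0.7 | 0.05 | 0.035 | 14% | 0.923 | 0.0855 |
| 0.7 | 0.10 | 0.070 | 28% | 0.809 | 0.1967 |

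With s = 0 there is no bias.

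**4. The realised wait.** The document ties the wait to the center, and center is already in the model. As a post-allocation covariate it probably adds little bias, and it also adds little beyond center.

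**The case against.** The strongest defence is that nothing arm-specific happens before T2. Triple P starts in the last third of CBT, so the assumed s would have to come from knowing about a future parenting course. An s of 0.05–0.10 SD is 20–40% of the whole expected effect and has no basis in the document. This stands: s may be zero.

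A reader might infer that the baseline rating itself is unblinded. The text does not show that. The rater is a teacher or caregiver, the form does not refer to the trial, and teacher ratings were chosen because ill parents' ratings can be biased. Only the patient is said to be told the arm, not every family member. What remains is that the patient's family forwards the T2 form, so its return could depend on the arm. The feedback session is undated and the flowchart (Figure 3) was not available here, so its place before T2 is read from the section in which it stands.

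T2 is also a deliberate choice: the Discussion explains that the double baseline relates change before treatment to change under treatment. That purpose needs assessments at T1 and T2. It does not need allocation at T1.

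A reader might further infer a power shortfall, since losses before Triple P dilute the contrast. The plan says "Taking a drop-out rate of 20 % into account"; if all of those losses came before Triple P, d would fall to 0.8 × 0.25 = 0.20, and an unadjusted t-test on 317 per arm would have power 0.710. The documents do not support this. It needs every loss to precede Triple P and every outcome still to be observed, whereas Sample Size treats drop-out as loss from the analysis. With baseline adjustment at r = 0.6 (residual SD 0.8), the same diluted effect has power 0.80 if d is on the change-score SD and 0.88 if on the score SD.

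Randomising only when the last third of CBT begins is not a remedy either. It would restrict the question to patients who stay in therapy that long.

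**Conclusion.** The point holds as one of timing. As written, allocation and its disclosure to the patient come before the wait. The T2 TRF, which is both the baseline and a covariate, and the realised wait are recorded afterwards. Families lost during the wait are randomised without a baseline.

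The size of any bias is unknown and may be nil. Under the assumed s of 0.05–0.10 SD and r of 0.3–0.7 it is 0.015–0.07 SD, or 6–28% of d = 0.25. The planned sample size is not in question. The case for change is that the risk can be removed cheaply for future families and examined for those already allocated.

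**What to change.** **Families not yet randomised.** Carry out the web randomisation, and tell the patient the arm, only after the T2 interviews are done and the T2 teacher forms are either returned or past a fixed return window. The stratification factors (center, comorbidity, number of children) are known by then. The planned N stays at 634, because d, α and power are unchanged, and no visit is added. Losses during the wait then occur before allocation.

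**Families already randomised.** Add a sensitivity analysis with T3 (and T4) TRF as outcome and T1 TRF in place of T2 TRF as covariate. Omit the realised wait, keep center, and add T1 TRF to the imputation model. The article does not say that T1 teacher forms must be back before randomisation, so record the return date and identify T1 forms returned after allocation.

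**Cost.** An amendment to the procedure and a short addition to the analysis text. Lead time for planning Triple P places becomes shorter, although the last third of a 6- to 12-month therapy begins about 4 to 8 months after T2 (two thirds of 6 to 12). The T1-based analysis will probably have a lower baseline–outcome correlation, and so less precision, because T1 lies further from T3.

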### Pre-assessment T2

After the usual waiting period for a psychotherapy treatment in the study centers (waiting period can differ between the study centers depending on their usual waiting periods for a psychotherapy treatment), structured clinical interviews for patients and children are conducted again with the patient respectively the same parent as in T1 (for each child separately). The family is invited to another session in which interviews about knowledge of mental disorders are conducted with each included family member, and codes for logging into REDCap at home to complete the questionnaires are handed out. The forms with REDCap-codes for the children's caregivers/teachers are also handed out to the family with the request to forward them to the respective caregivers/teachers.

### Treatment Period

All patients receive between 25 to 45 sessions of individual CBT. Patients allocated to the experimental intervention (CBT+Triple P) receive in addition 8 to 10 group or individual Triple P sessions parallel to the last third of the CBT sessions. After every therapy session, patients, and therapists complete a session-feedback screener including aspects of therapeutic alliance and symptom intensity, as well as on fidelity. (Serious) adverse events [(S)AE] are also assessed after every therapy session with a checklist. If a (S)AE occurs, a report has to be filed and send to the study coordination at the UMR. Every fifth session, the patients are also handed out a code for logging into REDCap at home to complete the BSI to assess remission status (early, late, and non-remitters).

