Data missing for the primary outcome variable will be replaced by using multiple imputation (68) which takes the covariates treatment group, center, number of comorbidities, number of children, baseline TRF score at T2, and length of waiting period between T1 and T2 (in weeks) into account by applying the fully conditional specification method (69). This will be realized using the option “FCS” of the SAS “MI” procedure implemented in SAS 9.4. Sensitivity analyses will be performed by applying alternative methods dealing with missing data such as complete case analysis. All secondary outcomes will be evaluated descriptively, and descriptive *p*-values are reported together with 95% confidence intervals for the corresponding effects. Further exploratory analyses will be performed to identify potential prognostic factors (e.g., parental disorder, child psychopathology, socio-economic status) and mediators (e.g., Brief Symptom Inventory/BSI, Parenting Questionnaire/EFB, Parental Stress Inventory/ESF) for an intervention effect. The safety analysis includes calculation of frequencies and rates of adverse and serious adverse events together with 95% confidence intervals. All analyses will be performed with SAS version 9.4 or higher.

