### Post-assessment T3

Using the same measurements as in the pre-assessments, the post-assessment is conducted by an assessor who is blind to the treatment condition. Structured clinical interviews for patients and children are conducted again with the patient, respectively the same parent as in T1 (for each child separately). During a separate session, interviews on knowledge about mental disorders are conducted with each included family member separately, (S)AE are assessed for every included family member, and codes for logging into REDCap at home to complete the questionnaires are handed out at the end. The forms with REDCap-codes for the children's caregivers/teachers are also handed out to the family with the request to forward them to the respective caregivers/teachers. If a (S)AE occurs, a report has to be filed and sent to the study coordination at the UMR.

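### Adverse-event checks follow every therapy session and only CBT+Triple P has extra sessions, so AE rates risk unequal ascertainment of unknown size

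*Protocol article*

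**What the plan says.** During treatment, AE collection is triggered by sessions (Treatment Period): "Serious) adverse events [(S)AE] are also assessed after every therapy session with a checklist". The same section sets the session numbers. For both arms, "All patients receive between 25 to 45 sessions of individual CBT". Patients in the experimental arm "receive in addition 8 to 10 group or individual Triple P sessions parallel to the last third of the CBT sessions". Interventions describes the CBT schedule as "weekly or bi-weekly sessions of individual state of the art Cognitive Behavioral Therapy", with higher frequency allowed.

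Limitations puts the assessment burden at "four extensive assessments for all family members as well as up to 55 therapy assessments".

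Table 1 also lists AEs at T2, at the intermediate assessments (patient) and at T3 and T4. At T3, "S)AE are assessed for every included family member", and "the post-assessment is conducted by an assessor who is blind to the treatment condition". Follow-Up-Assessment T4 repeats this.

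The analysis is given in one sentence of Statistical Methods: "The safety analysis includes calculation of frequencies and rates of adverse and serious adverse events together with 95% confidence intervals". It states no denominator for the rates.

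**The concern.** When AEs are found by asking, an arm that is asked more often can record more of them at the same true risk. Here the number of scheduled questions differs by design, because the add-on treatment brings its own contacts. Those contacts run alongside CBT, so they add questioning without adding planned observation time.

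AE frequencies and rates are the trial's planned safety description of an add-on to CBT. If CBT+Triple P shows more events, the reader needs to know whether that reflects extra harm or extra asking. The session checks are also not blinded: patients are told their arm, and therapists deliver the treatment. If the type of session at which an event surfaced is not recorded, no later analysis can separate the two explanations.

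**Working it through.** **Inputs.** CBT sessions c = 25 to 45 in both arms, and Triple P sessions t = 8 to 10 in the experimental arm only (Interventions; Treatment Period). One AE check per session (Treatment Period). Maximum of 55 therapy assessments (Limitations). AE assessments at T2, T3 and T4 in both arms (Table 1).

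**1. Reproduce the stated figure.** 45 + 10 = 55, which matches exactly. So Triple P sessions appear to be counted among the session-level assessments. The article does not say outright that they carry the AE checklist, but it does not exempt them.

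**2. Count scheduled checks at equal CBT dose.** The ratio of experimental to control is (c + t)/c. Adding T2, T3 and T4 gives (c + t + 3)/(c + 3). Within the last third of CBT it is (c/3 + t)/(c/3). For a per-session rate with equal numbers of events it is c/(c + t).

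| c | t | Session checks | With T2, T3, T4 | Last third only | Per-session rate, equal events |
|---|---|---|---|---|---|
| 25 | 8 | 33/25 = 1.32 | 36/28 = 1.29 | 16.33/8.33 = 1.96 | 25/33 = 0.76 |
| 25 | 10 | 35/25 = 1.40 | 38/28 = 1.36 | 18.33/8.33 = 2.20 | 25/35 = 0.71 |
| 45 | 8 | 53/45 = 1.18 | 56/48 = 1.17 | 23/15 = 1.53 | 45/53 = 0.85 |
| 45 | 10 | 55/45 = 1.22 | 58/48 = 1.21 | 25/15 = 1.67 | 45/55 = 0.82 |

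**3. Move from checks to recorded events.** This needs quantities the article does not give: an AE rate, the sensitivity and recall window of the checklist, and a denominator. Two illustrative models with assumed values, both with no true difference between arms, show the range.

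- *Each check has an independent chance q of a new report.* The ratio of patients with any report is [1 − (1 − q)^(c+t)] / [1 − (1 − q)^c]. Over the four rows above it is 1.173 to 1.393 at q = 0.001, 1.135 to 1.335 at q = 0.01, and 1.005 to 1.050 at q = 0.10.
- *Each check covers the time since the last visit.* It detects an event with probability s, and T3 recovers a share r of those missed. Events are spread evenly over treatment, and an event in the last third gets one extra check. With d0 = 1 − (1 − s)(1 − r) and d1 = 1 − (1 − s)²(1 − r), the ratio is (⅔·d0 + ⅓·d1)/d0. Results: 1.167 (s = 0.5, r = 0), 1.041 (s = 0.7, r = 0.5), 1.006 (s = 0.9, r = 0.8) and 1.000 (s = 1).

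One extra check per CBT interval is a simplification: t/(c/3) runs from 8/15 = 0.53 to 10/8.33 = 1.20.

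**4. Direction.** Per patient or per unit of time, the ratio is 1 or above in both models. Per session, with equal events, it is 0.71 to 0.85.

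**The case against.** The strongest reply is that more checks need not mean more recorded events. Triple P runs alongside CBT, so both arms are already questioned at CBT sessions over the same weeks. An event mentioned at a Triple P session would ordinarily come up at the next CBT session. T3 and T4 then give both arms the same AE assessment by an assessor blind to arm. All of this stands, and it is why the distortion may be small. It removes the imbalance only if each check captures everything since the last one, or if T3 recovers what was missed over a treatment that usually lasts 6 to 12 months.

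Three further points stand in part. First, the checklist at Triple P sessions, especially group sessions, is inferred. Second, the denominator and the handling of duplicate reports may be settled in the full protocol or SAP, so their absence from the article is no fault; unequal collection, however, is part of the design as the article describes it. Third, no between-arm AE test is stated, so any effect is confined to descriptive safety reporting.

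A reader might infer that the AE rates are biased against CBT+Triple P, by a factor of 1.18 to 1.40. The document does not support that. The factor requires detection proportional to the number of checks, the direction depends on an unstated denominator, and some excess could be a real effect of the added treatment.

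**Conclusion.** The point holds as a risk of unequal ascertainment, not as a demonstrated bias. On the article's own session numbers, CBT+Triple P has about 18% to 40% more scheduled session checks at equal CBT dose, and 1.53 to 2.20 times as many in the last third of CBT. This rests on Triple P sessions carrying the AE checklist and on similar CBT session counts in the two arms.

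The resulting distortion in AE rates cannot be computed from the document. For rates per patient or per unit of time, 1.18 to 1.40 is the upper bound. The illustrative recall model gives 1.00 to 1.17 over the values tried, so the true figure may be close to 1. A per-session denominator is not a neutral alternative, because it would favour the experimental arm.

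The primary teacher-rating analysis, its error control and the sample size are unaffected.

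**What to change.** - In the AE form, record the type of contact at which each event was first noted: CBT session, Triple P session, T3 or T4. The article does not show whether this field already exists.
- Report all-source AE rates per patient and per patient-month, not per session.
- Beside them, add a between-arm comparison restricted to the checks common to both arms (CBT sessions plus T3 and T4), and list events first noted at Triple P sessions separately. If such an event also appears on a later common check, keep that entry in the restricted comparison; otherwise the restriction over-corrects.
- Leave SAE reporting to the Data Safety Monitoring Board as it is.

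The cost is one eCRF field, one extra table and some SAP wording. The restricted comparison may omit genuine events linked to Triple P. It therefore supplements the all-source rates and must not replace them. With both shown, no safety data are lost, and a reader can see how much of any excess depends on the extra contacts.
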